### Sample Size Calculation

Based on the literature, in which approximately 81% of carious lesions were estimated to have been arrested with AgF [34], the community intracluster correlation was calculated as 0.09. Using these parameters at 80% power, α=.05, and 12 clusters available (6 clusters per treatment arm), the estimated sample size required is 320 in each arm. Allowing for a 25% loss to follow-up each year, the estimated sample size is 570 per arm, or 95 children and adolescents per cluster (rounded up). Sample size estimations were undertaken on STATA 15 (StataCorp) using the commands for cluster randomized trials for proportions of caries arrest.

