### Data Analysis

The trial has been registered in the Australian and New Zealand Clinical Trials Registry (ACTRN12622001066774p). All analysis will be reported according to CONSORT (Consolidated Standards of Reporting Trials) guidelines. Data analysis will use intention-to-treat approaches, with standard imputation measures used to manage missing data. The analysis plan for each aim is as follows.

Aim 1 (severity of dental disease in young Indigenous Australians): the severity of dental disease will be calculated using the decayed, missing, and filled tooth surface index (dmfs/DMFS) for the primary and permanent dentition. The 2014-2016 National Child Oral Health Survey will enable comparison with both general and Indigenous population-level estimates [1]. General analysis will comprise the chi-square and 1-tailed Student *t* tests within the study sample and a nonoverlapping 95% CI when comparing with population estimates.

Aim 2 (changes in dental disease following AgF intervention): the trial will be analyzed on an intention-to-treat basis according to group allocation. Generalized linear mixed models will be performed to determine differences in the primary outcome (arrest in dental caries) between the 2 groups and over time when the outcome is continuous. For binary outcomes, general estimating equations with the log binomial family will be used [35].

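### Aim 1 names a 1-tailed t test with no stated direction, tests that assume independent children, and an interval-overlap rule that is not a 5% test

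*Protocol article*

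**What the plan says.** The Data Analysis section of the protocol article measures Aim 1 by dmfs/DMFS. For comparisons inside the study it says: "General analysis will comprise the chi-square and 1-tailed Student" t tests. For the external comparison it says that "The 2014-2016 National Child Oral Health Survey will enable comparison with both general and Indigenous population-level estimates", and the criterion is "a nonoverlapping 95% CI when comparing with population estimates". It gives no direction, significance level or reason for the 1-tailed choice. It does not say which within-sample comparisons are meant, or whether the Aim 1 tests and intervals allow for community.

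The Sample Size Calculation section plans 12 clusters of 95 and reports that "the community intracluster correlation was calculated as 0.09", in a calculation about the proportion of caries arrested. For Aim 2, by contrast, the Data Analysis section names mixed models and estimating equations, both of which can carry clustering.

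**The concern.** There are three separate problems, and all lie in methods that the article names.

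- **Tail.** Aim 1 sets out to describe disease levels and has no directional hypothesis. A 1-tailed test needs a direction fixed beforehand, and none is given. The chi-square test is not described as 1-tailed, so the two named tests also work to different conventions.
- **Independence.** Ordinary chi-square and Student t tests treat every child as a separate observation. Children from one community resemble each other, and the sample size section itself allows for this.
- **Overlap rule.** Whether two 95% intervals overlap is not a 5% test of whether two values differ. Its error rate depends on the ratio of the two standard errors.

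At stake is whether the differences reported under Aim 1, within the sample and against the national survey, carry the error rate that a reader would assume.

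**Working it through.** **Inputs from the Sample Size Calculation section.** ICC 0.09; 12 clusters; 320 per arm before losses; 25% loss per year; 570 per arm; 95 per cluster. The article gives no numerical result for Aim 1, so the only figure to reproduce is the cluster size: 320/(1 − 0.25)² = 568.9 per arm, and 568.9/6 = 94.8, rounded up to 95, so 6 × 95 = 570. It reproduces.

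**Assumptions.** The ICC of 0.09 belongs to caries arrest. Its use for dmfs/DMFS is an assumption, so a range of 0.01 to 0.15 is shown. The survey's standard error is not given, so a range of ratios is shown.

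**1. Tail.** A 5% 1-tailed test with the direction picked after seeing the data has error 2 × 0.05 = 0.10. With the direction fixed in advance it is 0.05.

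**2. Contrasts between communities, tests unadjusted.** Design effect DE = 1 + (95 − 1) × ICC. Actual error is 1 − Φ(1.645/√DE) for the 1-tailed test and 2[1 − Φ(1.96/√DE)] for a two-sided or chi-square test. At ICC 0.09, DE = 1 + 94 × 0.09 = 9.46 and √DE = 3.08, so 1140 children carry the information of 1140/9.46 ≈ 121.

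| ICC | DE | 1-tailed | two-sided / chi-square |
|---|---|---|---|
| 0.01 | 1.94 | 0.12 | 0.16 |
| 0.05 | 5.70 | 0.25 | 0.41 |
| 0.09 | 9.46 | 0.30 | 0.52 |
| 0.15 | 15.1 | 0.34 | 0.61 |

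A simulation of 12 clusters of 95 at ICC 0.09 (20,000 runs, no pairing) gave 0.29 and 0.52.

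**3. Effect of pairing on arm contrasts.** One cluster per state goes to each arm, so variation between states cancels from the arm difference. If ρc is the part of the ICC that lies between communities within a state, the variance ratio is 95ρc + (1 − 0.09). With all of the ICC within states this is 8.55 + 0.91 = 9.46, as above. If half lies between states (an illustration), it is 95 × 0.045 + 0.91 = 5.19, its root is 2.28, and the errors are 1 − Φ(1.645/2.28) ≈ 0.24 and 2[1 − Φ(1.96/2.28)] ≈ 0.39.

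**4. Factors balanced within communities, such as sex.** The variance ratio is 1 − 0.09 = 0.91. The errors are 1 − Φ(1.645/0.954) = 0.042 and 2[1 − Φ(1.96/0.954)] = 0.040, slightly conservative.

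**5. Overlap rule.** Let r be the survey standard error divided by the correct study standard error. With valid intervals, error = 2[1 − Φ(1.96(1 + r)/√(1 + r²))]. If the study interval ignored clustering at DE 9.46, its half-width would shrink by 3.08 and the error would be 2[1 − Φ(1.96(1/3.08 + r)/√(1 + r²))].

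| r | valid intervals | study interval ignoring clustering |
|---|---|---|
| 0 | 0.050 | 0.52 |
| 0.1 | 0.032 | 0.41 |
| 0.25 | 0.017 | 0.27 |
| 1 | 0.006 | 0.066 |
| 2 | 0.009 | 0.042 |

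With valid intervals and equal standard errors, a difference that a 5% test would detect with 80% power is detected with power Φ(1.96 + 0.84 − 2.77) = 0.51.

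**The case against.** The strongest reply is that Aim 1 gets one sentence in a condensed article, and that variance estimation for a descriptive aim is commonly left to a fuller plan. That stands for the intervals: nothing says that they ignore clustering, so the last column of the second table is a conditional result, not a reading of the plan. It stands less well for the tests, because the article names particular ones whose standard forms assume independence. It does not touch the tail or the overlap rule, which are explicit.

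A reader might infer that Aim 1 testing as a whole runs at 30% to 52% error. The documents do not support that. Those figures apply only to contrasts between communities, rest on an ICC stated for another outcome, and are an upper bound at that ICC for arm contrasts because of the pairing. The text does not say that arms or states will be compared.

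A reader might also infer that the 1-tailed test is wrong in size as such, or that the overlap rule errs in both directions at once. A 1-tailed test with its direction fixed in advance has its nominal size. For the overlap rule, the strict and the loose case rest on opposite assumptions about the same interval, and either can come close to nominal for some survey standard errors.

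Finally, the Inclusion Criteria admit only children with active carious lesions. Their dmfs/DMFS can be expected to exceed survey values through selection alone, so a type I error against the survey matters less than how the difference is described. That point is fair and is taken into the fix.

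**Conclusion.** The point holds at moderate size. Three things are firm from the text: a 1-tailed t test for a descriptive aim with no direction, simple tests in a design that the article itself treats as clustered, and an overlap rule used as the criterion for a difference.

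The sizes are conditional. The tail choice turns 5% into 10% only if the direction is chosen after the data are seen. Unadjusted contrasts between communities would have error 0.30/0.52 at ICC 0.09, with a range of 0.12/0.16 to 0.34/0.61 over ICC 0.01 to 0.15; this assumes that an ICC of that order applies to dmfs/DMFS. The overlap rule runs from 0.6% to 5% with valid intervals. It would run from about 4% to 52% if the study interval ignored clustering, which the article does not state.

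Aim 1 is descriptive, and the primary comparison under Aim 2 is untouched.

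**What to change.** In the Aim 1 paragraph of Data Analysis:

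- Make the comparisons two-sided, with standard errors that allow for community as the sampling unit, state as stratum, and degrees of freedom suited to 12 clusters.
- Replace the overlap rule with the estimated difference from the survey value and its 95% CI, computed from both standard errors.
- State that this difference describes a sample selected for active caries, because the interval does not correct for that selection.

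The cost is a few sentences and no new data or design change. The price is wider intervals for contrasts between communities.

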### Outcomes

The primary outcome will be the arrest of carious lesions in the dentition, with arrested caries defined as nonpenetration by a dental probe. Secondary outcomes will include SEWB, OHRQoL, dental anxiety, and dental behaviors. A SEWB measure has been developed by our team based on community consultation, item polling, and a theoretical framework that identified six core SEWB domains for Indigenous Australian youths: (1) feeling empowered; (2) feeling strong in my body; (3) feeling loved and safe; (4) feeling resilient; (5) feeling strong in my mind; and (6) feeling strong in my identity. OHRQoL will be assessed using the Caries Impacts and Experiences Questionnaire [29], which we have validated and successfully implemented in other studies involving Indigenous Australian children [30]. Dental anxiety will be assessed using the Child Dental Anxiety and Scale [31], modified to capture anxiety from adolescent participants, which we have also validated and implemented in studies involving Indigenous children [30]. Behaviors will be assessed using items from the 2012-2014 National Child Oral Health Survey [1]. These will include participant age when commenced tooth brushing, tooth brushing frequency, use of fluoride toothpaste, last time participant saw an oral health care provider, usual reason for participant to visit an oral health care provider, and consumption of sugar-sweetened beverages and foods.

Effectiveness measures for the economic evaluation will include the number of children and young people managed in primary oral health care without the need for specialist referral, changes in SEWB, the numbers and types of treatments provided, and caries increments. A cost-utility analysis will be undertaken using the recently developed dental caries utility index for adolescents [32] and ECOHIS-4D to measure the utility values of the health states experienced by children and young people [33].

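### The log-binomial GEE named for binary outcomes needs stated small-sample inference and pair handling, because 12 communities in 6 matched pairs are too few for the usual sandwich z-test

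*Protocol article*

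**What the plan says.** All references are to the protocol article.

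- Outcomes: the primary outcome is lesion arrest, with "arrested caries defined as nonpenetration by a dental probe". At lesion level this is binary.
- Data Analysis, Aim 2: two methods are named. For a continuous outcome, "Generalized linear mixed models will be performed to determine differences in the primary outcome (arrest in dental caries"). For the other case, "For binary outcomes, general estimating equations with the log binomial family will be used".
- Sample Size Calculation: the trial is sized on proportions arrested, at "80% power, α=.05, and 12 clusters available (6 clusters per treatment arm"), with "the community intracluster correlation was calculated as 0.09" and "the estimated sample size required is 320 in each arm" before allowance for dropout.
- Study Design and Randomization: the clusters are matched in pairs, two per state or territory, and one of each pair is drawn as the immediate-intervention site.

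Aim 2 does not give the GEE cluster level, the variance estimator, the reference distribution, any small-sample correction or the role of the pairs.

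**The concern.** GEE sandwich inference is justified as the number of independent clusters grows. The 95 children planned per community do not help, because the relevant count is 6 communities per arm. With so few, the sandwich variance is biased downward and too variable for a normal reference. Separately, randomization within pairs means that the two arm means may be correlated, and an analysis without the pairs misjudges the variance of their difference. Run in default form, the analysis would give a primary p-value and confidence interval whose real error rate differs from the stated .05. The Introduction justifies this trial by its greater rigor and its aim of changing policy, so the error rate of the main comparison matters.

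**Working it through.** **Inputs from the article.** 12 communities, 6 per arm, 6 pairs; alpha .05 (taken as two-sided); intracluster correlation 0.09; 320 evaluable per arm, which is 320/6 = 53.3 per community; 25% loss per year.

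**The article's own figure.** 320/(0.75 × 0.75) = 568.9 per arm, or 94.8 per community. Rounded up to 95, this gives 6 × 95 = 570 per arm, which reproduces. The 320 cannot be checked because no control proportion is given. No attained type I error is stated.

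**Set-up.** Equal community sizes, with community-level rates treated as roughly normal. If the estimated variance has expectation *r* times the true variance, on *df* degrees of freedom, a z-test has size P(|t_df| > 1.96 × √r).

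**Case A: pairs ignored, no within-pair correlation.** The sandwich divides by 6 in each arm where 5 would be unbiased, so r = 5/6, with 10 df.
- Size = P(|t10| > 1.96 × √(5/6)) = P(|t10| > 1.789) = 10.4%.
- Beta-binomial simulation (40,000 replicates, correlation 0.09, 53 or 95 per community, arrest 0.4 to 0.81): 9.3-10.1%.
- Fitted log-link binomial GEE, exchangeable (1,500 replicates, 53 per community, arrest 0.5): 9.1%. With the variance multiplied by 12/10 and t on 10 df: 4.7%.

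**Case B: pair effects in the model, still uncorrected.** Let d_j be the six within-pair differences and S the sum of (d_j − mean)². The unbiased variance of the mean difference is S/30, on 5 df.
- Pairs as GEE clusters: the sandwich gives S/36, so r = 30/36 = 5/6 and size = P(|t5| > 1.789) = 13.4%.
- Communities as GEE clusters: the sandwich gives S/72, so r = 30/72 and size = P(|t5| > 1.265) = 26.2%.

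**Case C: pairs ignored, within-pair correlation ρ of community rates.** The true variance of the difference shrinks by (1 − ρ), but the sandwich does not see this. The ratio of the root-mean-square estimated SE to the true SE is √((5/6)/(1 − ρ)). The article gives no ρ, so these values are assumed. Sizes are from simulated normal community means.

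| ρ | SE ratio | Uncorrected z | Unpaired, corrected, t10 | Paired t, 5 df |
|---|---|---|---|---|
| 0 | 0.91 | 10.4% | 5.0% | 5.0% |
| 0.1 | 0.96 | 8.8% | 4.1% | 5.0% |
| 0.3 | 1.09 | 6.0% | 2.5% | 5.0% |
| 0.5 | 1.29 | 3.4% | 1.3% | 5.0% |

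A rate near 5% in the uncorrected z column arises only where two errors offset each other. A small-sample correction alone, without the pairs, becomes conservative as ρ rises. The paired analysis holds its level throughout.

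**Power.** Suppose the true difference gives 80% power on a z-test, so the noncentrality is 1.96 + 0.84 = 2.80. With the true variance unchanged, power is about 71% on t with 10 df and 61% on t with 5 df. Positive within-pair correlation returns some of this to a paired analysis, because the true variance falls by (1 − ρ).

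**The case against.** The strongest objection is that the fault is read from silence. The article is condensed. It names GEE and cites a reference; it does not say that the variance is uncorrected or the reference normal. GEE with a small-sample correction is still GEE, and such detail commonly sits in an analysis plan, which is not shown here. This stands: the article cannot be said to have chosen an invalid test.

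A reader might infer more strongly that the standard errors are too small and that the type I error is about 10%, twice the stated level. The documents do not support that. The 10% needs the pairs to be ignored and the within-pair correlation to be negligible, while the design is explicitly matched. Cases B and C show that the error can be larger or smaller, and that the standard error can be too large. Neither size nor direction follows from the text.

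It can also be said that GEE is not fixed as the primary analysis, since Aim 2 names the primary outcome in the mixed-model sentence, for a continuous version. That is fair, but the probe definition and the proportion-based sample size both point to the binary branch.

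What the objection does not remove is that a large-sample method is named for a 12-cluster trial, with nothing in the text to make it valid and no mention of the matching that the design relies on.

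**Conclusion.** The point holds in conditional form. On the article's own definition and sizing, log-binomial GEE is the likely primary analysis. With 12 communities in 6 pairs, its usual sandwich z-test is not a valid 5% test. The size is about 9-10% with pairs ignored and negligible within-pair correlation, and about 13% with pairs as clusters and pair effects. With pairs ignored and within-pair correlation of 0.3 to 0.5, it is about 6% to 3.5% with oversized standard errors. These figures assume equal community sizes and a two-sided test; the within-pair correlations are assumed because none is given. Whether the trial would actually run this form cannot be told from the article. If the analysis plan already states a correction and the handling of pairs, the point is met.

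**What to change.** State, before outcome data are analyzed, that the primary binary analysis respects the matched pairs and uses small-sample inference. Either of these would serve:

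1. A paired cluster-level analysis: the 6 within-state differences in arrest proportion, or in its log for a ratio, tested with t on 5 df.
2. GEE with community as the cluster, adjusted for state or territory, with a small-sample variance correction (Kauermann-Carroll or Mancl-DeRouen) and a t reference on between-cluster df net of the pair terms: 12 − 6 pair terms − 1 arm term = 5. With pair terms each community has leverage 7/12. In the equal-size case Kauermann-Carroll then gives r = (30/72)/(5/12) = 1, while Mancl-DeRouen gives (30/72)/(5/12)² = 2.4, which is conservative.

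An unpaired analysis with t on 10 df is not a full remedy, as the table shows.

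The cost is one or two sentences of text, wider confidence intervals (the 5-df critical value is 2.57 against 1.96), and lower attained power than a z-based calculation gives. The expected power should be restated on the chosen df. The paired cluster-level analysis also weights states equally unless weights are specified. Using Poisson in place of log-binomial, or Kenward-Roger df for continuous outcomes, is optional and not part of this point.

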### Ethical Considerations

Ethics approval (number 04-22-1013) has been obtained from the Aboriginal Health Council of South Australia Human Research Ethics Committee, the University of Adelaide Human Research Ethics Committee, the Human Research Ethics Committee of the Northern Territory Department of Health and Menzies School of Health Research, the Far North Queensland Human Research Ethics Committee, the Aboriginal Health and Medical Research Council of New South Wales Human Research Ethics Committee, the Australian Institute of Aboriginal and Torres Strait Islander Studies Human Research Ethics Committee, and the Western Australian Aboriginal Health Ethics Committee. Before being recruited, all participants will be required to sign an informed consent form, which includes consent for the authors to publish the findings in the peer-reviewed scientific literature. All authors are named investigators on the project; they all contributed to the intellectual input of the study design and in writing this protocol.

## Results

Participant recruitment for this study commenced in May 2023, and up until September 2023, around 540 children and young adults have been recruited. We anticipate the first results to be submitted for publication 2 years following initial recruitment.

## Discussion

### What are the Views of the Indigenous Community About the Study?

Feedback from multiple Indigenous participants in our current studies reveals that poor access to dental services is a key barrier to achieving optimal health. Many participants should be in the prime of their lives, yet ongoing concerns about their oral health are impacting important life decisions (eg, shame about poor oral health prevented one from singing in a television documentary, while embarrassment about bad breath prevented another from attending a job interview). These inequities begin in early childhood, with Indigenous children as young as 2 years old in some communities requiring all teeth to be removed under a hospital-based general anesthetic because of advanced dental decay.

### Why is This Study Important?

Despite the unacceptable poor oral health experienced by many Indigenous children and young people in regional and remote locations, there have been few interventions developed using culturally safe methodologies for improving oral health using low-cost approaches that are non–resource-intensive. Consequently, the management arsenal available to reduce the incidence of active dental decay among Indigenous children and young people that does not involve extensive restorative care (needles, drilling, and filling) is limited. The proposed study will investigate a novel use (AgF) for a potentially widely available public health service with which every health professional can become familiar. Currently, AgF is the only nonsurgical therapeutic option for the management of active dental caries. Our results may provide evidence for decision makers to make informed resource allocations in Indigenous oral health, which impacts both SEWB and health-related quality of life. This is especially necessary in the ACCHO sector.

### Strengths and Limitations

This study will test the hypothesis that Indigenous children and young people in 6 Australian states and territories can be provided with appropriate dental care in local Indigenous settings using the AgF approach without specialist intervention and avoiding the need for treatment under hospital-based general anesthesia. This study has six major strengths: (1) it will evaluate the and severity of dental disease in Indigenous children and young people in 6 states and territories; (2) it will test the efficacy of a simple and culturally safe AgF initiative, which could be easily implemented into the training program of Indigenous Health Workers to be included in their remit of care; (3) we will have capacity to comprehensively assess the cost-effectiveness of the intervention, meaning uptake into clinical guidelines will be much swifter than if no cost-effective analysis was undertaken; (4) the intervention will likely lead to SEWB improvements in Indigenous children and young people; an important strategic priority given current commitments to improving child health and well-being, with the Australian Government launching, in October 2021, the world’s first National Children's Mental Health and Well-Being Strategy [36]; (5) we have engaged and consulted considerably with participating ACCHOs, using their feedback to shape the research questions and; (6) our researchers are world-class experts in their respective specialties and have experience working with Indigenous child and adolescent populations. Limitations include operationalizing a national-level trial while COVID-19 is still present and assessing active dental caries by clinical examination only (no use of radiographs). Conducting a clinical trial in challenging contexts and following the cultural protocols of local Indigenous communities prevents us from blinding study participants.

In conclusion, our findings have the potential to change the way in which the oral health of Indigenous children and young people is managed, with desired impacts including cost savings on expensive dental treatments, improved SEWB, nutrition, social, and learning outcomes, and improved quality of life for both children and young people and their caregivers and the broader Indigenous community. This study addresses priorities raised in the National Aboriginal and Torres Strait Islander Health Plan 2013-2023 [37], particularly in regard to increasing understanding of Indigenous health issues at a community level, improving public health measures that address Indigenous health, and facilitating the collection of Indigenous health data.

